### Statistical analysis

For the analysis of the primary study parameter, a per-protocol analysis will be used. The sole criterion for inclusion in the analysis is that a participant has completed the initial tACS session and EEG recordings. Changes in relative delta power will be assessed using separate linear mixed models for standardised and personalised tACS compared with sham, with relative delta power as the dependent variable, time*group and study centre as fixed factors, and participant as a random factor. Data analysis will be performed blinded for treatment allocation. A significance level of p=0.05 (two-tailed) will be applied. To retain sensitivity to detect potential effects in this novel area of research, no adjustment for multiple comparisons will be made. In cases of deviations from the linear mixed model, robust models and non-parametric alternatives will be considered. Subgroup analysis will be conducted by including additional fixed factors to the mixed models, such as delirium aetiology, sex and age. Functional outcomes, along with other quantitative EEG measurements and cognitive outcomes, will be analysed using non-parametric or parametric tests depending on the distribution of scaled test results. Blinding success for participants as well as researchers will be tested using a χ^2^ test.

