
**Figure 1 F1:**
[figure not shown]
Study flow chart. EEG, electroencephalography; tACS, transcranial alternating current stimulation; T, treatment; V, visit.

**Table 1 T1:** Overview study procedures

Procedures (time needed)	Baseline visit (V1)	First treatment visit (T1)	Additional treatment visits (T2 up to T14)	Post-treatment visit (V2)	Follow-up visit (V3)
Medical history*	X				
Physical health*	X				X
Current medication use*	X	X	X	X	X
Clinical Frailty Scale*	X				
Sensation questionnaire (5 min)		X		X	
Blinding and subjective treatment experience (1 min)		X		X	
Feasibility questionnaire (5 min)		X			
Delirium interview (10 min)	X				
ICDSC (10 min)	X	X	X	X	
DOSS (5 min)†	X	X	X	X	
TICS-M (10 min)					X
EEG (40 min)	X‡	X		X	
tACS (30 min)		X	X		
Estimated total duration	25 or 60 min‡	95 min	45 min	65 min	15 min

* This information will be recorded as part of standard clinical care, and missing information will be requested via family and will therefore not require additional time.

† Only non-intensive care unit () patients will be assessed using the DOSS.

‡ Only the group randomised to personalised tACS will receive an EEG during the baseline visit.

DOSS, Delirium Observation Screening Scale; EEG, ElectroencephalogramICDSC, Intensive Care Delirium Screening Checklist; tACStranscranial altering current stimulationTICS-M, Telephone Interview for Cognitive status, modified version

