### Sample size and statistical power

The sample size calculation is based on data obtained from a previous study that examined EEG findings in both delirious and non-delirious patients.^15^ In this study, patients with delirium showed a median relative delta power of 0.59 (IQR 0.47–0.71), while those without delirium had a median of 0.20 (IQR 0.17–0.26), resulting in an effect size of 0.39 (0.20–0.59). This study excluded patients in whom the diagnosis delirium was not certain, which may have inflated the effect size. It is therefore anticipated that both standardised and personalised tACS will lead to a more modest decrease of 0.15 in relative delta EEG power poststimulation compared with prestimulation measurements. We hypothesise that personalised tACS may be superior to standardised tACS in reducing relative delta power. However, the lack of data to support this claim necessitates assuming equal effectiveness for both arms in the sample size calculation. Based on these assumptions, a sample size of 159 participants (ie, 53 per group) was estimated using G*Power 3.1. This estimation considered an effect size of 0.15 with a SD of 0.3, an alpha of 0.05 and 80% statistical power. Patients who do not complete the initial tACS session with EEG recordings will be replaced, as well as patients who withdraw consent.

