### Intervention

tACS will be administered to participants who are randomised using the Nurostym tES device (Brainbox, UK) by a trained member of the study team. The same tACS device and settings will be used across all three participating centres to ensure consistency of results. For all study arms, tACS will be administered at an intensity of 2.0 mA (peak to peak) for 30 min using two 5×5 cm saline-soaked electrodes while the impedance is kept below 10 kΩ. Electrode placement (described below) follows the 10–10 EEG system, ensuring consistent positioning of tACS electrodes across different stimulation days, patients and centres. The electrodes will be positioned beneath a 64-channel EEG cap. During the first treatment session, this cap will also be used for repeated EEG measurements, whereas on subsequent treatment days, it will serve solely as a reference for tACS electrode positioning. Treatment with psychoactive medication(s) that is deemed necessary for the participant will be continued as prescribed by the treating physician.

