#### Sham stimulation

The procedure for sham stimulation will be identical to either standardised or personalised tACS, except for the electrical current administered. After the 5-digit pin code is entered, which enables sham stimulation, the tACS device will ramp up to 2.0 mA peak to peak for 30 s, stimulate for 60 s and ramp down for 30 s to 0 mA. This mimics the perception of actual tACS stimulation and improves blinding. To evaluate the effectiveness of blinding, both the participant and the researcher will be asked to guess the group allocation after the first and last treatment session (online supplemental appendix 1).

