### Outcomes

#### Pilot study outcomes

During the pilot phase, data regarding the percentage of fully completed tACS sessions will be recorded as well as increased care requirements within 1 hour following tACS administration. An increase in care requirement is defined as a (medication-based) intervention (eg, for heightened agitation or skin issues resulting from the electrodes), fixation, or transfer to unit with more advanced care (eg, the intensive care unit). Furthermore, duration of delirium will be recorded as defined in the secondary outcomes below. On analysis of these findings, adjustments to the protocol may be proposed and will be submitted to the Medical Research Ethics Committee (MREC) for approval before the start of the main study phase, if deemed necessary.

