#### Main study primary outcome

##### Relative delta power

An 18-min resting state EEG recording will be conducted by a trained clinical researcher directly before and after the first tACS session. EEG recordings will be obtained using a 64-channel Biosemi ActiveTwo EEG system with active gel electrodes (Biosemi B.V., Amsterdam, Netherlands) at a sampling rate of 2048 Hz. Active electrodes, wherein each electrode has its own amplifier, are employed to reduce artefacts due to enhanced signal-to-noise ratio. EEG data will be visually inspected for eye movement and muscle artefacts. A minimum of 80 s of eyes closed artefact-free data will be analysed. Data will undergo FIR bandpass filtering in the following frequency bands: delta (0.5–4 Hz), theta (4–8 Hz), alpha (8–13 Hz), low beta (13–20 Hz) and high beta (20–30 Hz). Relative delta power will be calculated by dividing the total power within the delta frequency band (0.5–4 Hz) by the total power across frequency bands from 0.5 to 20 Hz. The upper limit of the frequency band is limited to 20 Hz to reduce the impact of muscle artefacts and high-frequency noise on the relative delta power calculation.^50^

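### The only stated primary analysis is limited to patients who complete the first session and its EEGs, a post-randomisation condition that can depend on the arm and leaves the comparison with sham open to selection bias

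*Protocol article*

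**What the plan says.** The Statistical analysis section of the protocol article states: "For the analysis of the primary study parameter, a per-protocol analysis will be used". It then defines the set: "The sole criterion for inclusion in the analysis is that a participant has completed the initial tACS session and EEG recordings". No analysis of all randomised patients is named for the primary outcome.

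The Sample size and statistical power section adds: "Patients who do not complete the initial tACS session with EEG recordings will be replaced, as well as patients who withdraw consent".

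Randomisation comes before the session on which inclusion depends. The footnote to Table 1 shows that allocation is already fixed at the baseline visit: "Only the group randomised to personalised tACS will receive an EEG during the baseline visit".

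Exposure to current differs by arm. Under Intervention, "tACS will be administered at an intensity of 2.0 mA (peak to peak) for 30 min". Under Sham stimulation, the device ramps up for 30 s and will then "stimulate for 60 s and ramp down for 30 s to 0 mA".

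**The concern.** Randomisation protects the comparison of the groups as they were allocated. Here a patient enters the primary comparison only after getting through the first session and both recordings. If the stimulation influences who gets through, the active and sham patients left in the analysis are no longer comparable by design. If those who drop out would also have shown a different change in relative delta power, part of the observed difference comes from selection. Replacement restores the numbers but not the comparability.

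At stake is the main efficacy claim of each active arm against sham. An EEG that was not recorded after an early stop cannot be recovered later. Recruitment began in April 2024 and the trial is expected to end in April 2027, so the choice affects data still to be collected.

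**Working it through.** **1. Inputs from the protocol article**

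- Planned effect 0.15, SD 0.3, alpha 0.05, power 80%, 159 patients or 53 per group (Sample size and statistical power).
- Two-sided test, active against sham, separately for each active arm (Statistical analysis).
- Active current: 30 min. Sham current: 30 s + 60 s + 30 s = 120 s, about 2 min.

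**2. The plan's own figure.** A three-group one-way ANOVA with f = (0.15/0.3)/2 = 0.25 and alpha 0.05 gives 53 per group, 159 in total, with power 0.805. The stated number is reproduced and is not at issue in this point. The 53 per group is used below only for the standard error.

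**3. Assumptions.** The document gives no completion rates and says nothing about how non-completers change. Assumed here:

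- non-completion is 10 or 15 percentage points higher on active than on sham (for example 15% v 5%, or 20% v 5%);
- the change in relative delta power is worse by D = 0.1, 0.2 or 0.3 in non-completers than in completers, equally in both arms;
- the true effect is zero;
- the SD of 0.3 applies to the change.

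**4. Bias.** In one arm with non-completion p, the mean of all randomised patients equals the completer mean plus p × D. The completer mean is therefore too favourable by p × D. Between arms:

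spurious benefit = (p_active − p_sham) × D

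**5. Type I error.** SE = 0.3 × √(2/53) = 0.0583. With r = bias/SE, the two-sided error is 1 − Φ(1.96 − r) + Φ(−1.96 − r).

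| Non-completion, active v sham | D | Bias | Share of 0.15 | r | Type I error |
|---|---|---|---|---|---|
| equal | any | 0 | 0% | 0 | 5.0% |
| 15% v 5% | 0.1 | 0.010 | 7% | 0.17 | 5.3% |
| 15% v 5% | 0.2 | 0.020 | 13% | 0.34 | 6.4% |
| 15% v 5% | 0.3 | 0.030 | 20% | 0.51 | 8.1% |
| 20% v 5% | 0.1 | 0.015 | 10% | 0.26 | 5.8% |
| 20% v 5% | 0.2 | 0.030 | 20% | 0.51 | 8.1% |
| 20% v 5% | 0.3 | 0.045 | 30% | 0.77 | 12.1% |

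If non-completers had the better change (D negative), the same sums would give a bias against active stimulation.

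**6. Does the planned mixed model solve this by itself?** With two time points and a random intercept, a patient with only a pre-session EEG informs the baseline mean. That patient affects the estimated change only through a baseline difference between completers and non-completers. Where the baselines are alike and only the unseen change differs, nothing is corrected. A simulated check with 4,000 patients per arm, a zero true effect and equal baselines gave these time-by-group estimates:

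| Scenario | Completers only | Pre-only records kept | All post-EEGs observed |
|---|---|---|---|
| 15% v 5%, D = 0.2 | −0.0327 | −0.0326 | −0.0112 |
| 20% v 5%, D = 0.3 | −0.0378 | −0.0374 | 0.0059 |

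Keeping pre-only records moved the estimate by less than 0.001. Observing the post-session EEG removed the assumed bias of 0.020 or 0.045, apart from simulation error.

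**The case against.** The strongest objection is that unequal completion is assumed. Sham uses the same ramp to 2.0 mA and is meant to feel like stimulation. The cap and the pre- and post-session EEGs are common to all arms. The one obstacle to completion that the article itself names is the EEG requirement, in its strengths and limitations. The pilot also assesses the share of fully completed sessions, and its results go to the ethics committee before the main phase. This stands as a limit on size and certainty. It does not answer the design point, because the pilot check leaves the analysis set unchanged and the exposure to current still differs fifteenfold (30 min v 2 min).

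The direction is also open. The outcome is a within-patient change, so a calmer baseline in completers would largely cancel. Nothing in the document says that non-completers change for the worse. This stands too.

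Some stronger readings are tempting but not supported:

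- *The protocol expects stimulation to cause stopping.* The words "for heightened agitation or skin issues resulting from the electrodes" are examples within a definition of extra care needed in the hour after a session. They are not reasons for ending one, and sham patients wear the same electrodes.
- *Recruitment continues until each arm has 53 completers.* The text says only that patients are replaced. It does not describe replacement within arms.
- *The EEG quality rule leaves a gap.* The article says "A minimum of 80 s of eyes closed artefact-free data will be analysed". Whether a shorter usable recording counts as incomplete is a detail that an article may leave to the full protocol or analysis plan.
- *The randomised comparison is lost.* It is weakened to an unknown degree, and possibly not at all.

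**Conclusion.** The concern holds as a risk of bias. The plan fixes a primary analysis set that depends on a post-randomisation event, replaces those who fail it, and states no all-randomised analysis beside it. The difference in exposure to current gives a plausible route to unequal completion.

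The document cannot settle size or direction. With the assumed 10 to 15 point gap and D of 0.1 to 0.3, the spurious benefit is 0.010 to 0.045, that is 7 to 30% of the planned 0.15. Type I error is about 6% for 15% v 5% with D = 0.2, and about 12% for 20% v 5% with D = 0.3. It is nil if non-completion and its reasons are balanced. A completer analysis can be of mechanistic interest, but the stated objective is efficacy, tested against sham, and that rests on the randomised groups.

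This should be fixed, with moderate confidence. It is not a demonstrated failure of the trial.

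**What to change.** Change the primary analysis as follows:

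1. The primary set is all randomised patients with a pre-stimulation EEG, analysed in the arm to which they were randomised, whether or not the session was completed.
2. The post-session EEG, already in the schedule, is recorded also when stimulation stops early, where the patient allows it. Most of the gain comes from this step.
3. Patients may still be replaced, but those replaced stay in the primary set, subject to consent.
4. The completer analysis is kept as supportive.
5. Outcomes that remain missing are examined in a missing-not-at-random sensitivity analysis, because the mixed model alone does not correct for them.

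The cost is a change of wording, some additional EEG recordings and a few more records in the model. The drawback is a slightly diluted estimate if incomplete sessions work less well. Some patients will refuse the second recording, so the bias may be reduced rather than removed.

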When applying tACS as a potential treatment for delirium, the most straightforward approach is to apply tACS in the alpha frequency range, targeting both reduced alpha power and functional connectivity seen in delirium.^15^,^18^ However, numerous approaches in terms of stimulation location and frequency are possible, which might be equally or more effective in treating delirium than alpha-tACS. Incorporating functional brain connectivity changes of individual patients into personalised treatment could improve treatment effectiveness, reduce adverse effects, decrease the need for trial and error in clinical trials and enhance our understanding of the mechanisms underlying treatment effects.^37^ The use of computational models may allow one to infer how modifications of neuronal properties might influence emergent neuronal activity and treatment response.^38^ A promising type of computational model is the neural mass model, which models brain activity of large populations of neurons.^39^ Using a network of coupled neural masses, neuronal activity similar to an encephalopathic EEG has been simulated.^40^ Building on this, this study will apply neural mass modelling of individual functional connectivity changes in a virtual trial to optimise treatment settings.

In the current trial, we will evaluate whether tACS normalises brain activity, specifically relative delta power, in delirium. To date, no randomised controlled trials (RCTs) investigated tACS as treatment for delirium, highlighting significant gaps in our understanding of the feasibility, effectiveness and the most effective application strategies. Therefore, the trial will begin with a pilot phase aimed to assess feasibility. On successful completion of the pilot phase, the main study phase will commence with three study arms to assess the efficacy of tACS in reducing relative delta power: a standardised treatment arm, a sham control arm and a personalised treatment arm based on a computational model and virtual trial. We hypothesise that both standardised and personalised tACS will decrease relative delta power compared with sham tACS in delirium patients. By adopting this two-step approach, this study aims to evaluate the feasibility as well as the effectiveness of tACS in patients with delirium.

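### The primary analysis has two separate arm-v-sham models with about 72% power each; one pre-specified active-v-sham contrast would test the general tACS question with about 84% under the plan's own assumption

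*Protocol article*

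**What the plan says.** The protocol article poses the question at two levels. The Introduction puts it for the treatment as a whole: "In the current trial, we will evaluate whether tACS normalises brain activity, specifically relative delta power, in delirium". The Abstract states its aim in the same general way. The hypothesis at the end of the Introduction and the Study objectives section then put it for each active arm against sham.

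Sample size and statistical power expects both forms of tACS to "lead to a more modest decrease of 0.15 in relative delta EEG power poststimulation compared with prestimulation measurements". It adds: "We hypothesise that personalised tACS may be superior to standardised tACS in reducing relative delta power". Because data are lacking, this "necessitates assuming equal effectiveness for both arms in the sample size calculation". The result is "a sample size of 159 participants (ie, 53 per group) was estimated using G*Power 3.1", from "an effect size of 0.15 with a SD of 0.3, an alpha of 0.05 and 80% statistical power".

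Statistical analysis specifies "separate linear mixed models for standardised and personalised tACS compared with sham", with time by group and centre as fixed factors and participant as random factor. "A significance level of p=0.05 (two-tailed) will be applied", and the plan openly declines to adjust for multiple comparisons. The main study has no three-arm test and no comparison of active with sham overall. The only active-v-sham comparison is the interim analysis after the pilot. It has a single active arm and does not test delta power.

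**The concern.** Each planned model leaves out about a third of the patients, and both reuse the same sham group. The question about tACS in general is left to be read off two overlapping tests, and no rule says whether success needs either arm or both. Counting either as success raises the error rate above 5%, and requiring both takes power well below 80%. If the two results disagree, or both narrowly miss, the plan has no pre-specified statement on tACS as such, although the patients needed for one are already in the trial.

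**Working it through.** **Inputs.** From Sample size and statistical power: difference 0.15, SD 0.3 (d = 0.15/0.3 = 0.5), 53 per arm, 159 in total. From Statistical analysis: two-sided 5% per test, no adjustment. From the randomisation section: 30 pilot patients at 1:1, then 129 at weights 3:4:1:2 (standardised active, personalised active, standardised sham, personalised sham). Two assumptions: SD 0.3 is the SD of the pre-to-post change, because it is paired with a pre-to-post decrease; and the mean change under sham is zero, because none is given.

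**The plan's own figure.** A one-way ANOVA F-test with three groups, f = d/2 = 0.25, 5% alpha and 80% power needs 158, rounded up to 159 (80.5% power at 159). The article does not name the test, so this match is an inference. The planned two-arm comparison does not give 53: it needs 64 per arm (t distribution). For the assumed pattern of effects (0, 0.15, 0.15), f = 0.5 × √2/3 = 0.236; the F-test at 159 then has 75.4% power and would need 177.

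**Power of the two kinds of contrast** (noncentral t):

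| Contrast | SE | Effect/SE | Power | Difference detectable with 80% power |
|---|---|---|---|---|
| One active arm v sham, 53 v 53 | 0.3 × √(2/53) = 0.0583 | 2.57 | 72.2% | 0.165 |
| Both active arms v sham, 106 v 53 | 0.3 × √(1/106 + 1/53) = 0.0505 | 2.97 | 84.0% | 0.142 |

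**Joint behaviour of the two planned tests** (simulation, 400,000 trials, 53 per arm, d = 0.5 in both active arms): both significant 58.5%, exactly one 27.5%, neither 14.0%. With no effect in either arm, at least one is significant in about 9.0%. With the overall contrast as a third unadjusted test, this becomes about 9.6%.

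**What the overall contrast adds to the verdict.** In the same simulation it is significant when neither arm is in 1.8% of trials. It misses although at least one arm is significant in 3.8%.

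**Including phase.** Expected main-phase numbers are 129 × 0.3 = 38.7, 129 × 0.4 = 51.6, 129 × 0.1 = 12.9 and 129 × 0.2 = 25.8. The pilot adds 15 standardised active and 15 standardised sham. It therefore supplies 15/105.3 = 14% of active and 15/53.7 = 28% of sham, which is why phase belongs in the model. Stratified by phase, the information is 15 × 15/30 + 90.3 × 38.7/129 = 7.5 + 27.09 = 34.59; effect/SE = 0.5 × √34.59 = 2.94; power is about 83%.

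**Pathway mix.** Over the whole trial, the standardised pathway makes up 53.7/105.3 = 51% of active and 27.9/53.7 = 52% of sham. Within the main phase it is 38.7/90.3 = 43% against 12.9/38.7 = 33%.

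**Unequal effects.** The overall contrast tests the average of the two effects.

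| Effects in the two active arms | Average | Power of overall contrast |
|---|---|---|
| 0.15 and 0.15 | 0.150 | 84.0% |
| 0.15 and 0.10 | 0.125 | 69% |
| 0.15 and 0.075 | 0.1125 | 60% |
| 0.15 and 0 | 0.075 | 31.5% |

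Power falls below 80% once the second effect is about 0.134 or less.

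**If 0.3 is the SD at one time point**, the change has SD 0.3 × √(2(1 − r)), where r is the pre-post correlation, which the article does not give. Power per arm and overall is then 58% and 70% at r = 0.3, 72% and 84% at r = 0.5, and 91% and 97% at r = 0.7.

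**The case against.** The strongest reply is that the plan does what its hypothesis says. The hypothesis and objectives are worded per arm, so separate arm-v-sham models are legitimate. That stands: a reader might infer that the analysis contradicts the trial's question, but the general wording and the per-arm wording sit side by side, and the models answer the second.

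Next, equal effectiveness is a device for sizing the trial, adopted for lack of data and next to a hypothesis that personalised tACS may be superior. The average of a fixed 10 Hz montage and a strategy still under development is no treatment that a patient would receive. This also stands, and it is why the contrast cannot replace or gate the arm-specific results.

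Third, setting 84% against 72% flatters the contrast. At least one planned test succeeds in about 86% of trials under the same assumption, and the contrast rescues only 1.8%. That is correct, but the 86% is bought at an error rate of about 9%. The gain is one 5% test of the overall question.

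Fourth, a third unadjusted test would worsen the multiplicity (9.0% to 9.6%), and at alpha 0.025 the contrast has only 76% power. This is a fair objection to adding it without a named role; the fix has to give it one.

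Finally, an extra contrast could sit in an analysis plan that is not shown. But the article states the primary analysis positively, and its stated 80% power does not belong to that analysis.

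**Conclusion.** The point holds in a limited form. With the plan's own inputs, each planned comparison has about 72% power, not 80%. The overall contrast is the only between-arm contrast above 80% (about 84%, or about 83% stratified by phase). This rests on equal effects of 0.15, SD 0.3 for the change, and 53 evaluable patients per arm, which the replacement rule supports.

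Two stronger readings are not supported. A reader might infer that the trial is likely to end with discordant arms. Under the plan's assumption the likeliest result is that both are significant (about 59%); exactly one (28%) and neither (14%) together make up about 42% before rounding. A reader might also infer that pooling compares groups with nearly the same mix of standardised and personalised pathways. That is true of the crude totals (51% v 52%) but not once phase is included (43% v 33% in the main phase), so pathway balance is no argument for the contrast.

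**What to change.** Fit one mixed model to all three arms, with phase (pilot or main) added to the planned terms and allowed to affect the pre-to-post change. Pre-specify the contrast 'mean of the two active arms minus sham' in that change as the single 5% test of the overall tACS question.

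Keep standardised v sham and personalised v sham. Do not make them conditional on the overall test. Report them as arm-specific estimates with confidence intervals, and state that each has about 72% power at 53 per arm. State also that the overall contrast has about 84% power if both effects are 0.15, about 60% if one is half that, and about 32% if only one arm works.

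The cost is a change of wording and one contrast, with no extra patients, visits or measurements. Recruitment is under way and the expected end is April 2027, so it should be fixed before any main-phase allocation is unblinded. The one real downside is dilution when the arms differ, and keeping the arm-specific results covers that.

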Delirious patients who meet all inclusion criteria but none of the exclusion criteria for eligibility and randomisation will be randomised to one of the study arms. Randomisation will be conducted electronically via the Castor Electronic Data Capture (EDC) study management system (Castor, Ciwit B.V., Amsterdam, the Netherlands), using a validated block randomisation model, stratified by study centre. In the pilot phase, standardised active tACS and sham carry equal weight (1:1). Patients will be randomised with block sizes of 2 and 4. In the main study phase, four groups will be created in Castor EDC (standardised active, personalised active, standardised sham, personalised sham) with different weights, depending on the number of participants who have been randomised to the active and standardised sham groups during the pilot phase. As the first 30 patients are included during the pilot phase, randomisation weights will be 3, 4, 1 and 2, respectively. These numbers are chosen to closely match the overall 1:1:1 allocation. Randomisation will be performed with block sizes of 10 and 20, which are randomly selected.

Following randomisation, a designated study team member not involved in any other study procedures or data analysis will be aware of the randomisation outcome. This person will have access to a list of codes that permits the tACS device to deliver active or sham stimulation. Participants and all other study staff will be blinded to whether active or sham stimulation is applied. To ensure blinding during the intervention, the monitor displaying the raw ECG traces will be covered with cardboard paper before the start of the procedure for patients on continuous ECG monitoring. Due to the additional EEG required in the personalised treatment arm, blinding with regard to receiving standardised or personalised tACS will not be possible. However, EEG preprocessing and data analysis will be performed blinded for treatment allocation.

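### The planned time-by-group model is a t-test on change in which study centre cancels; adjusting for baseline delta power would be more precise, by an amount that depends on an undocumented pre-post correlation

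*Protocol article*

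**What the plan says.** All references are to the protocol article.

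- **Model.** Statistical analysis specifies separate linear mixed models for standardised and for personalised tACS against sham, "with relative delta power as the dependent variable, time*group and study centre as fixed factors, and participant as a random factor". Baseline relative delta power is neither a covariate nor constrained to be equal across arms.
- **Data.** Under Main study primary outcome, the EEG is recorded immediately before and after the first session. Statistical analysis admits only participants who completed that session and its recordings, so every analysed participant has a complete pair.
- **Test.** "A significance level of p=0.05 (two-tailed) will be applied", and "no adjustment for multiple comparisons will be made".
- **Randomisation.** It is "stratified by study centre" (Informed consent, randomisation and blinding).
- **Sample size.** Both active arms are expected to give a change that "will lead to a more modest decrease of 0.15 in relative delta EEG power poststimulation compared with prestimulation measurements". "This estimation considered an effect size of 0.15 with a SD of 0.3, an alpha of 0.05 and 80% statistical power", and "a sample size of 159 participants (ie, 53 per group) was estimated using G*Power 3.1". The section does not say whether 0.3 is the SD of a change or of a single recording, and it gives no pre-post correlation.
- **Active arms.** The same section adds: "We hypothesise that personalised tACS may be superior to standardised tACS in reducing relative delta power". It then notes that data are lacking and assumes equal effectiveness.

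**The concern.** The model looks as if it handles baseline and accounts for the stratification factor. With two complete time points it does neither for the contrast that matters.

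Three things follow:

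- Precision is lost in both primary comparisons, although the baseline EEG is already recorded.
- If the arms differ at baseline by chance, regression to the mean carries part of that difference into the estimated effect.
- A reader will believe that centre has been adjusted for when it has not.

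The section declines multiplicity adjustment in order to keep sensitivity. Baseline adjustment also raises sensitivity, without spending any type I error.

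**Working it through.** **1. The planned model reduces to a t-test on change.** Write Y(i,t) = arm-by-time mean + centre effect + participant intercept + error, for t = pre, post. For each participant, post minus pre removes everything constant within the participant, which includes the intercept and the centre main effect. With complete pairs and a participant variance not estimated at zero, the time-by-group coefficient is the difference in mean change.

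This was checked on simulated data with 53 per arm and three centres that differed in level. In one set the mixed model with centre gave −0.13929 (SE 0.05258, t = −2.649). Without centre it gave −0.13929 (SE 0.05258). The t-test on change gave −0.13929 (t = −2.649). Two further sets agreed in the same way.

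**2. Precision forgone.** Assume equal pre and post SDs σ and correlation r.

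- Variance of change: 2σ²(1 − r).
- Residual variance of post given pre: σ²(1 − r²).
- Ratio of adjusted to change-score variance: (1 + r)/2, which is at most 1. The price is one degree of freedom.

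With unequal SDs, adjustment is still no less precise in large samples. The gain vanishes when the slope of post on pre is 1.

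**3. The plan's own sample size.** The stated inputs give d = 0.15/0.3 = 0.5. A three-group omnibus F-test with f = d/2 = 0.25 and alpha 0.05 gives N = 159 exactly, with power 80.5%. The planned test is pairwise and two-sided. With change SD 0.3, SE = 0.3 × √(2/53) = 0.0583 and noncentrality = 0.15/0.0583 = 2.574. On 104 df, power is 72.2%.

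**4. Power after baseline adjustment** (n = 53 per arm, two-sided 0.05, change SD 0.3, equal SDs; r is an assumption):

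| r | (1 + r)/2 | residual SD, 0.3√((1 + r)/2) | power |
|---|---|---|---|
| not adjusted | – | 0.300 | 72.2% |
| 0.3 | 0.65 | 0.242 | 88.5% |
| 0.5 | 0.75 | 0.260 | 83.8% |
| 0.7 | 0.85 | 0.277 | 79.0% |
| 0.8 | 0.90 | 0.285 | 76.7% |
| 0.9 | 0.95 | 0.292 | 74.4% |

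Simulation with 20,000 runs gave 83.8%, 78.5%, 76.3% and 74.4% at r = 0.5, 0.7, 0.8 and 0.9.

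**5. Sensitivity to the meaning of 0.3.**

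- If 0.3 is the SD of a single recording, power goes from 57.7% to 76.2% (r = 0.3), 72.2% to 83.8% (0.5) and 90.9% to 94.6% (0.7).
- The quoted IQR of 0.47 to 0.71 implies a single-recording SD of 0.24/1.349 = 0.178 if roughly normal. The change-score test then already has 86% power at r = 0 and 99% at r = 0.5.

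**6. Chance imbalance.** With equal SDs, a baseline difference Δ between arms shifts the change-score estimate by (1 − r)Δ in size. With SD 0.178, one standard error of Δ is 0.178 × √(2/53) = 0.035. At r = 0.5 the shift is 0.017, or 12% of the target 0.15. Two standard errors give about 23%.

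**7. Adding a phase term.** The pilot has no personalised arm. Take 15 standardised and 15 sham in the pilot, and 38, 38 and 53 (personalised) in the main phase. The phase effect is estimated within the standardised and sham arms with variance (1/15 + 1/38)/2 = 0.0465, in units of the residual variance. It enters personalised–sham with weight 15/53, which adds (15/53)² × 0.0465 = 0.0037 to 2/53 = 0.0377. The inflation factor is 1.099. Standardised–sham is unchanged. Under the assumptions of step 4, personalised–sham power with phase included is about 80% (r = 0.5), 75% (0.7) and 73% (0.8).

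**The case against.** The strongest reply is that the planned analysis is valid. Under randomisation the change-score contrast is unbiased, and the choice lies between accepted methods. That stands: the cost is efficiency, plus a conditional shift when baselines happen to differ.

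Three stronger readings are tempting, and the documents do not support them.

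- **That baseline adjustment recovers most of a power shortfall.** The protocol gives no pre-post correlation, does not say what 0.3 is the SD of, and gives no basis for assuming equal variances. With change SD 0.3 and equal SDs, adjustment reaches 80% only up to r of about 0.66. With the SD implied by the IQR there is no shortfall to recover. The gap itself comes from a sample size that reproduces as an omnibus test while the analysis is pairwise, which is a separate matter.
- **That a phase term can be added at no cost.** Step 7 shows that it costs about 10% in variance for personalised–sham.
- **That omitting personalised against standardised contradicts the trial's hypotheses.** The Introduction and Study objectives frame the hypotheses against sham. The sample size section says only that superiority is possible and assumes equality. Nothing says that the two active arms will be compared by their p values. An estimate of this contrast would be useful, but its absence from the primary models is not an error.

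**Conclusion.** The concern holds as a point about efficiency. The stated model is a t-test on change, the centre term has no effect on the primary contrast, and the baseline EEG is not used to best effect. These conclusions follow from the design alone: two time points, complete pairs and a random intercept whose variance is not estimated at zero.

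The size of the gain is conditional. If 0.3 is the SD of change and the pre and post SDs are equal, power at 53 per arm rises from 72% to about 84% (assumed r = 0.5), 79% (0.7) or 77% (0.8). For a 0-to-1 outcome, r = 0.7 and 0.8 would then need single-recording SDs of 0.39 and 0.47, and no such outcome can have an SD above 0.5. If the true SD is nearer 0.18, power is already ample and the benefit is narrower intervals and protection against chance imbalance.

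**What to change.** Replace the primary model by an ANCOVA of post-stimulation relative delta power with baseline relative delta power, arm and centre as covariates. An alternative is a mixed model with a common baseline mean across arms and centre-by-time, with variances allowed to differ between the two times. A plain random intercept forces them equal and so is not in general equivalent to ANCOVA.

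Preferably fit one three-arm model. Keep standardised–sham and personalised–sham as the primary contrasts, and report personalised–standardised as a secondary estimate with its 95% confidence interval.

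Decide separately, and before unblinding, whether to include study phase. It guards against drift between pilot and main phase, at the cost of about 10% more variance for personalised–sham.

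The protocol should also state whether 0.3 is the SD of change or of a single recording, and which pre-post correlation is assumed.

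The cost is a change of wording in the protocol and analysis plan and one degree of freedom for the baseline covariate (plus those for centre). All variables are already collected and the trial is still recruiting.
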